## Abstract

**Background:**

Acupuncture is effective for reducing the symptoms of neck pain (NP). However, the underlying mechanisms are not fully elucidated. Based on evaluating the efficacy of two acupuncture prescriptions for treating NP, this study aims to investigate the potential central mechanism of acupuncture treatment for NP by functional magnetic resonance imaging (fMRI).

**Methods:**

This is a randomized controlled trial; 86 patients will be randomly assigned into two acupuncture treatment groups at a ratio of 1:1. The whole study period includes 2 weeks baseline, 2 weeks treatments, and 12 weeks follow-up (4 and 12 weeks after treatment). The pain severity, the neck disability index, the cervical range of motion, and the pressure pain threshold, etc., will be used to evaluate the clinical efficacy of two acupuncture prescriptions for NP treatment. The MRI scans will be performed to detect cerebral activity changes of 20 patients in each group. The clinical data and MRI data will be analyzed, respectively. *Pearson* correlation coefficient will be used to evaluate the association between changes of cerebral activity features and improvement of clinical symptoms.

**Discussion:**

The results will provide further evidence for the clinical application of acupuncture in the treatment of NP.

**Trial registration:**

Chinese Clinical Trial Registry ChiCTR2000040930. Registered on 16 December 2020.

**Supplementary Information:**

The online version contains supplementary material available at 10.1186/s13063-021-05507-y.

## Background

Neck pain (NP), as a common musculoskeletal disorder, has become an important healthcare and social problem due to its high prevalence and heavy economic burden [1]. It is estimated that more than 30% of the population suffer from NP each year [2], and its lifetime prevalence in adults ranges from 14.2 to 71% [3]. Due to the increasing prevalence of NP, the health care costs of NP have rapidly increased [4–6].

In the United States, the cumulative annual treatment costs for lower back pain and NP is about $ 87.6 billion [7]. The treatment of NP has been challenging, because its etiology is complex and the symptoms are easy to recur. Although medications (e.g., muscle relaxants and non-steroidal anti-inflammatory drugs) can effectively alleviate acute pain, their side effects, including hepatotoxicity, etc., cannot be ignored [8]. Therefore, more patients tend to purchase non-drug therapies to relieve symptoms.

Acupuncture has been used to relieve pain for thousands of years in China. As early as 1997, the National Institutes of Health (NIH) recommended acupuncture treatment for pain disorders. Evidence from recent large-scale clinical studies has confirmed that acupuncture can effectively improve NP symptoms [9–14]. However, the underlying mechanisms of acupuncture for NP have not been fully elucidated.

Advances in neuroimaging techniques have enhanced studies into the central mechanisms of acupuncture as an analgesic in vivo. In the last two decades, many neuroimaging studies have been performed to elucidate the mechanisms of acupuncture analgesia, and achieved gratifying results [15–18]. For example, an fMRI study on migraines found that acupuncture was effective in improving abnormally reduced functional activity in the rostral ventromedial medulla/trigeminocervical complex area of patients [19]. Recently, significant alterations in the brain structure and function of NP patients have been reported by neuroimaging studies. Compared to healthy subjects, NP patients shown decreased functional activity in the left sensorimotor cortex and right temporoparietal junction [20], as well as increased functional connectivity between the right dorsolateral prefrontal cortex and the right anterior insula, which are associated with pain intensity [21]. Based on these findings, neuroimaging techniques appear to be useful tools for investigating the central mechanisms of acupuncture therapy for NP. Therefore, by MRI, this study aims to (1) evaluate the therapeutic effects of different acupoints prescription on NP, (2) investigate the changes in cerebral activity elicited by acupuncture treatment, and (3) analyze the possible correlations between the improvement of clinical symptoms and changes in brain activity, so as to explore the potential central mechanism of acupuncture for NP.

## Methods and design

### Study design

This is a randomized controlled trial. This protocol is reported in accordance with the Standard Protocol Items: Recommendations for Intervention Trials (SPIRIT) guidelines (supplementary file 1) and follows the principles of the Consolidated Standards of Reporting Trials (CONSORT) and the Standards for Reporting Interventions in Clinical Trials of Acupuncture (STRICTA) [22, 23]. The protocol has been approved by the Institutional Review Board of the Hospital of Chengdu University of Traditional Chinese Medicine (approved number: 2020KL-007) and registered at Chinese Clinical Trial Registry (registration number: ChiCTR2000040930, protocol version number: V1.0).

This study period last for 16 weeks, which included a 2-week baseline period, a 2-week intervention period, and a 12-week following period. A total of 86 patients with NP will be randomly assigned to the two acupuncture groups with a 1:1 ratio. Twenty patients in each group will be randomly selected to undertake MRI scans. Clinical outcome evaluation and MRI scans will be conducted at baseline and after treatment. The study procedure is outlined in Fig. 1 and Table 1.

**Fig. 1 Fig1:**
[figure not shown]
Flowchart of the procedure through the trial. The randomized controlled trial will enroll 86 eligible patients and divide them randomly into two groups at a 1:1 ratio. Twenty patients from each group will be randomly selected for MRI data collection. During the 2-week treatment, the patient will receive 6 acupuncture treatments. Clinical assessment will be performed at 4 time points: baseline, end of treatment, and 6 and 14 weeks after completion. The MRI scans will be performed at baseline and after treatment. Abbreviations: MRI magnetic resonance imaging

**Table 1 Tab1:** Study schedule for data collection

Period	Baseline		Treatment						Follow-up	
Assessment		1						2	3	4
Time (week)	0	2	3			4			8	16
**Pick-up information**										
Inclusion/exclusion criteria	√									
Informed consent	√									
Vital signs	√									
Medical history	√									
Physical examination	√							√		
**Acupuncture intervention**										
Group A (*n*=43)			√	√	√	√	√	√		
Group B (*n*=43)			√	√	√	√	√	√		
**Clinical assessment**										
VAS	√	√						√	√	√
NDI		√						√	√	√
ROM	√	√						√	√	√
PPT		√						√	√	√
SF-36		√						√	√	√
MSUS		√						√		
SAS and SDS		√						√	√	√
MRI (*n*=40)		√						√		
Laboratory test		√						√		
Adverse event								√		

This is a randomized controlled trial of neuroimaging including a 2-week baseline period, a 2-week treatment period, and a 12-week follow-up period. At baseline, patients will be screened based on inclusion and exclusion criteria; eligible individuals will then sign informed consent and undergo a physical examination. After being randomized into 2 groups, 6 acupuncture treatments will be performed for 2 weeks. Clinical data will be evaluated at baseline, after treatment ends, and at 4 and 12 weeks after completion; MRI scans will be performed at baseline and after treatment. After the treatment, laboratory tests will be performed, including routine blood test, C-reactive protein, and erythrocyte sedimentation tests. Adverse events will be recorded in the CRF at any time during treatment. Abbreviations:MRI magnetic resonance imaging, VAS visual analogue scale, NDI neck disability index, ROM range of motion, PPT pressure pain thresholds, MSUS musculoskeletal ultrasound, SF-36 Short-Form 36-Item Health Survey, SAS Self-rating Anxiety Scale, SDS Self-rating Depression Scale, CRF case report form

### Participants

#### Recruitment strategy

Patients will be recruited at the outpatient of the Hospital of Chengdu University of Traditional Chinese Medicine (TCM) and Sichuan Integrated Medicine Hospital. In addition, patients will also be recruited from the community and campus of Chengdu University of TCM through advertising (posting notices, distributing leaflets, web publishing). Patients who agree to participate in this study will be diagnosed by an orthopedic specialist. The eligible patients will be screened by the research assistant based on the inclusion and exclusion criteria.

#### Inclusion criteria

Participants who match the inclusion criteria will be included: (1) patients with NP as the main complaint and a visual analog scale (VAS) score of pain severity exceeding 4 points but less than 10 points (range 0–10 points), (2) for a duration of ≤ 3 months, (3) aged 18–60 years, and (4) agreeing to sign informed consent.

#### Exclusion criteria

Participants with any of the following conditions will be excluded: (1) they are pregnant or lactating women; (2) they have any organic or metabolic diseases of the digestive, hematopoietic, endocrine, or immune systems, or other severe primary diseases; (3) they have fibromyalgia and other central sensitization pain syndromes; (4) they have local skin damage or severe skin diseases that affect acupuncture manipulation; (5) they combine with mental or neurological diseases; (6) they have received acupuncture for NP within 1 month; (7) they have MRI contraindications, such as heart pacemaker, metallic foreign bodies, or severe claustrophobia, etc.; or (8) they are participating in other clinical trials.

#### Sample size

This study aims to compare the difference of the clinical efficacy of two acupuncture prescriptions (group A and group B). According to the results of the pilot study, the average reduction of VAS score in group A was 2.86±0.99, and the average reduction of VAS score in group B was 2.14±0.99. According to the formula, $$ n=\frac{2{\sigma}^2}{{\left(\mu 1-\mu 2\right)}^2}\times {\left({\mu}_{\alpha /2}+{\mu}_{\beta}\right)}^2 $$, with *α* = 0.05 (both sides) and 1 − *β* = 0.80 [24]. The sample size of each group was calculated to be 34, considering a 20% dropout rate; the final sample size was set to 43 per group, making the total of 86 in this study.

There is no widely accepted method for sample size calculation in neuroimaging study. Referring to the previous study [25], 15 participants in each group are the smallest size in neuroimaging studies. Considering a 20% dropout rate and the unavailability of data due to various reasons, this study will randomly select 20 patients from each group for MRI scans.

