### Randomization

Randomization will be carried out in two steps: (1) an independent, blinded statistician will generate a random allocation sequence using SPSS 26.0 (IBM, Chicago, IL, USA). The 86 patients will be randomly assigned into group A and group B at a ratio of 1:1; (2) 20 patients in each group will be randomly selected for MRI according to another random sequence. Allocation concealment will be achieved by sequentially numbered, opaque, sealed envelopes.

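### The printed inputs and 80% power give 30 per group, not 34, so at least one figure in the sample-size statement is wrong; the error is conservative

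*Protocol article*

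**What the plan says.** The Sample size section of the protocol article sizes the trial on the VAS comparison between the two acupuncture prescriptions. From a pilot study it reports that "the average reduction of VAS score in group A was 2.86±0.99, and the average reduction of VAS score in group B was 2.14±0.99". It prints the normal-approximation formula for comparing two means, with alpha 0.05 on both sides and 1 − β = 0.80. The result is then given as "The sample size of each group was calculated to be 34, considering a 20% dropout rate", and the final size is set at 43 per group and 86 in total.

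The resulting size is used throughout. The abstract says that "86 patients will be randomly assigned into two acupuncture treatment groups at a ratio of 1:1", and the Study design section, the Fig. 1 caption, Table 1 (43 in each group) and the Randomization section carry the same numbers.

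**The concern.** Every quantity that the formula needs is printed in one paragraph, so a reader can put the numbers in and should arrive at 34. The result is 30. A stated power and a stated sample size that do not belong together mean that one of the planning figures is false as printed.

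This paragraph is the only justification given for the size of the clinical comparison. If the power is misprinted, the reader is given the wrong design power. If the SD or the means are misprinted, the published pilot effect is wrong, and others may use it to plan their own trials. If n is wrong, more patients were planned than the stated reasoning requires.

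**Working it through.** **Inputs, all from the Sample size section**
- Difference in mean VAS reduction: 2.86 − 2.14 = 0.72
- SD, the same in both groups: 0.99
- Alpha 0.05 two-sided: z = 1.95996
- Power 0.80: z = 0.84162
- Allocation 1:1 (also in the Randomization section)
- Dropout 20%

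**Step 1. The plan's dropout step.** 34/(1 − 0.20) = 42.5, so 43 per group and 86 in total. This reproduces, and it shows that 34 is the number before dropout.

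**Step 2. The plan's formula with the plan's inputs.**
n = 2σ²/(μ1 − μ2)² × (z_α/2 + z_β)²
- 2 × 0.99²/0.72² = 1.9602/0.5184 = 3.7813
- (1.95996 + 0.84162)² = 7.8489
- n = 3.7813 × 7.8489 = 29.68, so **30 per group**, against 34 stated

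**Step 3. Can another reading at 80% power give 34?**

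| Variant at 80% power | n per group |
|---|---|
| t distribution instead of normal | 30.67, so 31 |
| One-sided alpha 0.05 | 23.4, so 24 |
| Least favourable rounding of the pilot figures (SD 0.995, difference 0.71) | 30.8, so 31 |
| 34 read as already including dropout, 30/0.8 | 37.5, so 38 |
| The same with the cruder inflation, 30 × 1.2 | 36 |
| Worst-case Wilcoxon efficiency, 29.68/0.864 | 34.4, so 35 |

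None gives 34. The two dropout readings would also leave 43 unexplained, and the document states no Wilcoxon allowance.

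**Step 4. What would give 34?**
- Power 0.85 with the printed pilot values: (1.95996 + 1.03643)² = 8.978, and 3.7813 × 8.978 = 33.95, so 34.
- Power 0.80 with difference 0.72 and an SD between about 1.04 and 1.06. For example, SD 1.05 gives 2 × 1.05²/0.72² × 7.8489 = 33.4, so 34.
- Power 0.80 with SD 0.99 and a difference between about 0.67 and 0.68. For example, 0.68 gives 2 × 0.99²/0.68² × 7.8489 = 33.3, so 34.

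**Step 5. Power on the printed inputs**

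| Evaluable per group | Normal | t |
|---|---|---|
| 30 | 80.4% | 79.1% |
| 34 | 85.1% | 84.0% |
| 43 (no dropout) | 92.1% | 91.5% |

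**Step 6. Size after dropout if 80% and the printed inputs were meant.** 30/0.8 = 37.5, so 38 per group and 76 in total. With the t distribution, 31/0.8 = 38.75, so 39 per group and 78 in total. The plan has 43 and 86.

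**The case against.** The strongest reply is that nothing in the trial suffers. On the printed inputs, 34 evaluable patients per group exceed the stated 80% power, and 86 randomised patients meet it even after 20% dropout. Allocation, endpoint, analysis and interpretation are untouched. A margin of four evaluable patients per group is also small beside the uncertainty of a pilot SD whose study size is not given: an SD about 6 to 7% larger would absorb it. All of this stands. It limits how serious the point is, but it does not make the printed calculation correct. Nor does the shortness of a journal article help, because the calculation is given in full rather than left out.

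Three stronger readings are tempting, and the document does not support them:
- **That 85% was the intended power.** It is the simplest reconciliation, since only one printed figure has to change. But the protocol article names 85% nowhere, and a misprinted SD or difference explains 34 equally well. Replacing 0.80 with 0.85 unchecked could put a wrong figure in place of a right one.
- **That ten patients too many are randomised.** The figure 86 − 76 = 10 holds only if 80% was the true target, every printed pilot value is right, and the bare normal approximation is taken as the requirement. With the t distribution the excess is 86 − 78 = 8.
- **That the design power is unknowable or the trial underpowered.** The text states 80%, and the planned number achieves it on the printed assumptions.

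**Conclusion.** The sample-size statement is wrong as written. With a difference of 0.72, SD 0.99, two-sided alpha 0.05 and 80% power, the printed formula needs 30 per group (31 with t), not 34. That is four patients per group, or about 13% above the figure that the formula gives. At least one of power, SD, means or n is misprinted or miscalculated, and only the sponsor can say which.

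The direction is conservative. If the pilot values are right, 34 evaluable per group give about 85% power (84% with t), so the trial is not underpowered on its own assumptions. This is a core planning figure that should be corrected, but it does not threaten the validity of the trial. The conclusion rests only on the formula and inputs in the Sample size section, and no rounding of those inputs removes the gap.

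**What to change.** Keep the 86 patients. Retrieve the original calculation and make the paragraph agree with it, in whichever of these ways applies:
1. If the printed pilot values are right and 34 was the calculated result, restate the power as 0.85.
2. If the power was 80% and the pilot values were misprinted, print the SD and means actually used and show that they give 34.
3. If 80% power with the printed inputs was meant, report that the formula needs 30 evaluable and 38 randomised per group, and that the planned 43 per group exceeds this.

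The power should not be chosen afterwards simply because it fits 34. The cost is a check of the original working and a correction of about one sentence. None of the three routes changes enrolment, so the 86 and the 43 per group given elsewhere in the article can stay as they are, although recruitment is already under way.

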### Randomization

Randomization will be carried out in two steps: (1) an independent, blinded statistician will generate a random allocation sequence using SPSS 26.0 (IBM, Chicago, IL, USA). The 86 patients will be randomly assigned into group A and group B at a ratio of 1:1; (2) 20 patients in each group will be randomly selected for MRI according to another random sequence. Allocation concealment will be achieved by sequentially numbered, opaque, sealed envelopes.

### Blinding

In this study, the patients, outcome assessors, and statistical analysts will be blinded. The patients will be treated in separate rooms to reduce communication. However, due to the particularity of acupuncture manipulation, blinding operator cannot be achieved.

### Interventions

Patients in group A will receive acupuncture at three acupoints (*Lieque* (LU7), *Chize* (LU5), and neck tenderness point on the affected side) (Fig. 2A). The acupoints of group B (control group) will receive acupuncture at three acupoints (*Shaohai* (HT3), *Lingdao* (HT4), and neck tenderness point on the affected side) (Fig. 2B). Tenderness points will be detected using a PX25 hand-held pressure pain tester (Wagner FPX™ 25).

**Fig. 2 Fig2:**
[figure not shown]
Locations of acupoints. **A** Locations of acupoints (group A). *Lieque* (LU 7), on the radial side of the forearm, above the styloid process of the radius and 1.5 cun above the horizontal stripes of the wrist. *Chize* (LU 5), in the transverse elbow, the radial side of the biceps tendon is sunken. **B** Locations of acupoints (group B). *Lingdao* (HT 4), in the anterior area of the forearm, the radial side of the ulnar carpi flexor tendon is 1.5 cun above the transverse stripes of the carpal palm. *Shaohai* (HT 3), at the midpoint of the line between the medial end of the transverse line of the elbow and the medial epicondyle of the humerus

The acupuncture manipulations are as follows: disposable sterile filiform needles (0.30 × 40 mm, Huatuo Medical Instrument Co., Ltd., China) will be inserted into acupoints at a depth of 20–30 mm after skin disinfection, and the Deqi sensation (a sensation of acid distension or numbness, or other acupuncture sensation) will be achieved [26]. Then, the HANS-200A acupoint nerve stimulator (Nanjing Jisheng Medical Technology Company, Nanjing city, China) will connect LU7 and LU5 of group A or HT3 and HT4 of group B respectively in the two groups for 30 min with dilatational waves (2–100 Hz, 1 mA). Patients will receive a total of 6 sessions of acupuncture in two weeks, with 3 sessions per week.

Acupuncture treatment will be performed by acupuncturists who have held a practitioner license for more than 3 years.

### Concomitant medications

Patients will be instructed not to take any other analgesic medications for NP during this study. In cases of severe NP, ibuprofen (300 mg per capsule with sustained release) will be allowed as rescue medication and should be recorded on the case report form (CRF). Patients are also asked to report to the researchers if they take any concomitant medications during the study, and to record the name, dose, and date of the medications used.

### Outcomes

The measurements will be conducted by independent assessors who have been trained before the study. The primary outcome is the change of VAS scores at baseline and after the end of treatment. VAS scores range from 0 to 10, with 0 indicating no pain and 10 indicating pain is unbearable. The secondary outcome measurements include neck disability index (NDI), Short-Form 36-Item Health Survey (SF-36), Self-rating Anxiety Scale (SAS), Self-rating Depression Scale (SDS), range of motion (ROM), and pressure pain threshold (PPT) will be evaluated at baseline, after treatment, and at 4 and 12 weeks after the end of treatment. In addition, we will perform musculoskeletal ultrasound (MSUS) before and after treatment. Among them, NDI is the most widely used clinical tool for self-assessment of disability caused by NP [27]. The SAS and SDS are the commonly used psychometric tools to measure the severity of anxiety and depression [28, 29]. SF-36 is a general health-based survey of quality of life, which can be self-administered by the patient with reliability [30]. ROM is one of the quantitative outcomes assessing the extent and degree of joint motor impairment. The changes of the tenderness threshold can quantitatively reflect the improvement of the pain severity [31]. Meanwhile, MSUS is an important method for clinical diagnosis of rehabilitation medicine, tracking disease progression and assessing curative effect [32].

### Patient safety

Adverse events during the study period will be reported in the CRF. The record should include the time, reason, clinical symptoms, signs of the adverse event, and the corresponding emergency treatment plan, as well as abnormal laboratory tests with clinical significance. In addition, all events will be evaluated for their relevance to the intervention and severity, according to the clinician.

### MRI data acquisition

The resting-state fMRI (RS-fMRI) will be performed at the baseline and the end of treatment, respectively. Patients will be asked to do not drink tea, coffee, or alcohol, avoid strenuous exercise, and ensure adequate sleep before the scan.

Patients will undergo RS-fMRI scan with a 3.0T MR scanners (Siemens 3T Tim trio, Erlangen, Germany) at the West China Hospital of Sichuan University. Patients will be asked to stay awake and to keep their heads still during the scan, with their eyes closed and ears plugged. Scans will be performed with the following procedures: localizer, three-dimensional T1-weighted imaging (3D-T1WI), blood oxygenation level-dependent fMRI (BOLD-fMRI) and diffusion tensor imaging (DTI) sequence. The 3D-T1WI scanning parameters will be as follows: repetition time (TR) = 6.008 ms, echo time (TE) = 1.7 ms, data matrix = 256 × 256, field of view (FOV) = 256 × 256 mm^2^. The BOLD-fMRI scanning parameters will be as follows: 31 contiguous slices with a slice thickness of 5 mm, TR = 2000 ms, TE = 30 ms, FOV = 240 × 240 mm^2^, Matrix = 64 × 64, flip angle (FA) = 90°, total volumes = 240. The DTI data will be acquired using a single-shot echo planar image sequence with the following parameters: FOV = 256 × 256 mm^2^, TR = 8500 ms, matrix = 128 × 128, slice thickness = 2 mm with no gap. Two diffusion-weighted sequences were acquired using gradient values b = 1000 s/mm^2^ and b = 0 s/mm^2^ with the diffusion-sensitizing gradients applied in 64 non-collinear directions.

